### Recruitment {15}

Clients will be recruited through professional therapeutic networks across participating cities. The principal investigator has conducted preliminary site visits to psychotherapy clinics in selected Pakistani capital cities to establish collaborations. Patient recruitment will follow a consecutive rolling enrollment strategy at each participating clinic. All prospective patients will undergo:An initial diagnostic interview for MDD symptomatology verification.Comprehensive eligibility assessment using study criteria.

Recruitment will continue sequentially until the target sample size (*n* = 80) is achieved, with an anticipated enrollment rate of 8–10 clients per month. Immediately following selection, participants will begin their allocated treatment (online or in-person EMDR). This consecutive enrollment and immediate treatment initiation process will be maintained consistently across all study sites until complete sample acquisition.

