**Fig. 2 Fig2:**
[figure not shown]
Research framework of study

Phase two (Quantitative Experimental Pilot Phase) shows the pilot testing process among a sample of *n* = 25. It includes baseline (T01), mid-treatment (T02), and end-of-treatment (T03) assessments, capturing dimensions of feasibility, acceptability, symptom measures, and client satisfaction. Phase three (Final Experimental Trial) includes a sample of *n* = 80 selection and allocation, repeated assessments (T01, T02, and T03), and ends with the outcomes box, summarizing the study’s outcomes such as clinical effectiveness, process quality, implementation outcomes, and symptom trajectories. Arrows between phases of the study highlight the sequential progression in the study from protocol development through pilot testing to full trial evaluation.

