### Clients selection and sample size {14}

The study focuses on individuals with MDD in Pakistan, specifically selecting geographically accessible participants residing in the major cities of Rawalpindi, Islamabad, and Peshawar. Recent literature cites various studies such as by Ishtiaq et al. [56], Noor et al. [57] and Umar et al. [58] on the high prevalence of depressive disorders in these three cities of Pakistan. However, since the exact number of MDD cases in these three major cities is unknown, a more customized, multi-stage sampling procedure has been adopted.

Initially, three rehabilitation centers located in the selected cities will be randomly but purposively picked for recruiting patients. The centers will not be chosen fully at random; rather, the characteristics of the vicinity and patient flow into centers will be considered. Within each selected center, clients will be recruited using a sequential consecutive sampling technique with a rolling enrollment strategy. This approach involves selecting every eligible patient who meets the inclusion criteria until the required sample size is achieved [59]. The estimated sample size of (*n* = 80) was calculated by using the below given approximation method for two independent group means, as recommended in the existing literature by Sakpal [60] and Chow [61]:$$n=\frac{\left({Z}_{\frac{\alpha }{2}}+{Z}_{\beta }{)}^{2}\cdot (2{\sigma }^{2}\right)}{\left({M}_{1}-{M}_{2}{)}^{2}\right.}$$where.

*n*= is the estimated sample size.

Zα/2 = is the Z-score matching to the desired α level (for e.g., 1.96 for 95% confidence).

Z*β* = is the Z-score matching the desired power level (for e.g., 0.84 for 80% power).

σ^2^ = is the pooled variance of two groups.

µ​_1_ - µ​_2_= are the expected difference in means of depression scores.

A two-sided significance level of α = 0.05 was selected, consistent with conventional recommendations for clinical trials, resulting in α/2 = 0.025 and a corresponding Z-score of 1.96. Statistical power was set at 80% (1 − β = 0.80), yielding β = 0.20 and a corresponding Z-score of 0.84.

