Based on previously published depression trials utilizing the Hamilton Depression Rating Scale-17 [62], a pooled standard deviation (σ = 8 points, variance = 64) for change scores was assumed. An expected mean difference of five points of the scale between the two treatment groups was specified, representing a clinically meaningful difference in depressive symptom severity. Substituting these values into the formula:$$n=\frac{\left(1.96+0.84{)}^{2}\times (2\times {8}^{2}\right)}{{5}^{2}}$$$$n=\frac{7.84\times 128}{25}$$$$n=40$$

Hence, the estimated sample size required was 40 clients per treatment arm, resulting in a total sample size of 80 clients. Furthermore, to account for potential attrition, a dropout rate of 15% was assumed, consistent with longitudinal psychotherapy trials. The adjusted recruitment target was calculated using the formula:$${n}_{\mathrm{initial}}=\frac{{n}_{\mathrm{target}}}{1-r}$$$${n}_{\mathrm{initial}}=\frac{80}{0.85}=94$$

Accordingly, approximately 94 clients will be recruited to ensure that at least 80 participants complete the trial and are available for primary analysis.

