## Assignment of interventions: allocation

### Sequence generation {16a}

A covariate-adaptive randomization (minimization) approach with a random element will be employed to allocate participants in a 1:1 ratio to the intervention arms. This method is specifically designed to maintain balance across key prognostic variables in trials with moderate sample sizes and multiple baseline covariates, while preserving allocation unpredictability [64, 65]. Randomization will be implemented centrally using a pre-specified Python-based algorithm, executed by an independent research assistant following completion of baseline assessments. The algorithm evaluates imbalance across predefined covariates—including study site, gender, baseline depression severity, and psychiatric comorbidity—and assigns participants to the treatment arm that minimizes overall imbalance, with a probabilistic element (i.e., less than 100% deterministic assignment) to reduce predictability. This approach avoids the limitations of excessive stratification and fixed block randomization while ensuring transparent, reproducible, and auditable allocation. A detailed description of the randomization algorithm, operational procedures, and audit trail is provided in Supplementary File A, and Fig. 3 presents the CONSORT flow diagram illustrating participant allocation.

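### The sample-size section recruits about 94 clients to secure 80 completers, but the recruitment rule stops at 80, which leaves about 68 completers and about 73% power

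*Protocol article*

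**What the plan says.** The protocol article, Clients selection and sample size {14}, sets out a two-group comparison of means. Its inputs are:

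- Significance level: "A two-sided significance level of α = 0.05 was selected".
- Power: 80%.
- Variability: "a pooled standard deviation (σ = 8 points, variance = 64) for change scores was assumed".
- Effect: "An expected mean difference of five points of the scale between the two treatment groups was specified".

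The result is 40 per arm, 80 in total. The section then allows for 15% dropout, divides 80 by 0.85, and states that "approximately 94 clients will be recruited to ensure that at least 80 participants complete the trial". In that section 80 is therefore the number who finish and can be analysed, and 94 is the number who enter.

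Two other places use 80 as the number who enter:

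- Recruitment {15}: "Recruitment will continue sequentially until the target sample size (*n* = 80) is achieved". The same sentence gives an expected enrolment of 8–10 clients per month.
- Research framework of study, text with Fig. 2: phase three "includes a sample of *n* = 80 selection and allocation".

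The Abstract (Methods) and the Discussion also give 80 as the size of the trial, in summary form. The figure of 94 appears only in the sample-size section.

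**The concern.** The Recruitment section is the instruction a site would follow when deciding whether to enrol the next client. As written, it closes enrolment at the number that the sample-size section needs at the end of treatment, after losses. The dropout allowance, calculated a few paragraphs earlier, then disappears.

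The trial would start with 80 and finish with fewer, so the stated 80% power would not be delivered even if every design assumption were right. Trial status describes recruitment as under way, and clients who were not enrolled cannot be replaced at the analysis stage.

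**Working it through.** **Inputs, all from the protocol article.** Difference 5 points; SD 8; two-sided alpha 0.05 (z = 1.96); power 80% (z = 0.84); dropout 15%. These come from Clients selection and sample size {14}. Sequence generation {16a} plans "to allocate participants in a 1:1 ratio to the intervention arms".

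**1. Reproduce the plan's figures.**

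- Per arm: n = (1.96 + 0.84)² × 2 × 8² / 5² = 7.84 × 128 / 25 = 40.14. The plan states 40.
- Total: 2 × 40 = 80.
- Inflated for dropout: 80 / 0.85 = 94.1. The plan states 94.

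Strict rounding up would give 41 per arm, and 95 for the inflated total. These differences are trivial and form no part of this point.

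**2. Completers under each enrolment number** (N × 0.85).

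- Enrol 94: 94 × 0.85 = 79.9, the required 80 to within rounding.
- Enrol 80: 80 × 0.85 = 68, or 34 per arm, which is 80 − 68 = 12 short.

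**3. Power on the plan's own inputs.** Power = Φ(5 / (8 × √(2/n)) − 1.96), with n completers per arm.

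| Enrolled | Completers | Per arm | 5 / (8√(2/n)) | Minus 1.96 | Power |
|---|---|---|---|---|---|
| Plan's calculation | 80 | 40 | 2.795 | 0.835 | 79.8% |
| 94 | 79.9 | 39.95 | 2.793 | 0.833 | 79.8% |
| 80 | 68 | 34 | 2.577 | 0.617 | 73.1% |

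Stopping at 80 costs 79.8 − 73.1 = 6.7 percentage points.

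**4. Interim trigger.** Interim analyses {21b} places the second look at 60 clients with end-of-treatment evaluations and calls this 75% of the target.

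- Against 80 completers (94 enrolled): 60 / 80 = 75%, as stated.
- Against 68 completers (80 enrolled): 60 / 68 = 88%.

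**5. Recruitment window.** Trial status gives April 1, 2025 to the end of February 2026, which is 11 months.

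- At 8 per month: 8 × 11 = 88, and 94 would take 94 / 8 = 11.75 months.
- At 10 per month: 10 × 11 = 110, and 94 would take 94 / 10 = 9.4 months.

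**The case against.** The best defence is that 80 in the Recruitment section is shorthand for completers. The dropout formula labels 80 as the target and 94 as the initial number, and the Recruitment section reuses the word target. The interim section also counts 60 clients with end-of-treatment data as 75% of 80, which fits that usage.

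This reading is possible, but the wording does not support it well. The Recruitment sentence ties 80 to a monthly enrolment rate and says nothing about completion. The research framework text applies 80 to selection and allocation, which precede any dropout. Completion is also known only after 10–14 weekly sessions, so a rule that literally waited for 80 completers would enrol beyond 94.

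A second defence is that Methods for addressing non-adherence and missing data {20c} keeps all randomised clients in the intention-to-treat analysis through multiple imputation. It is true that 68 is the number of completers and not the size of that analysis set. Imputation does not restore the information lost with the missing outcomes, however, and the sample-size section itself asks for 80 completers available for the primary analysis.

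A reader might infer three stronger things that the documents do not support:

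- **That the interim trigger is also wrong because it treats 80 as the final number.** It counts clients with end-of-treatment data, so 60 of 80 agrees with the sample-size section and with 94 recruited.
- **That the recruitment window shows 94 to be feasible, so that only wording is at stake.** The lower end of the window is 88, below 94. If sites are working to 80, the change means treating more clients.
- **That the low power for the 3-point non-inferiority margin is a result of this conflict.** Assuming no true difference and SD 8, that power is about 39% with 40 per arm and 34% with 34 per arm. Nearly all of the shortfall comes from sizing the trial on 5 points, which is a separate matter.

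**Conclusion.** The conflict is real. One section recruits about 94 so that 80 complete; the section that governs enrolment stops at 80, and the research framework text allocates 80. If the Recruitment section is followed, about 68 clients complete (34 per arm), and power on the plan's own inputs is about 73%, not the stated 80%.

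This size rests on the plan's assumed 15% dropout, equal losses in the two arms, a 5-point difference and an SD of 8. It is conditional: the documents do not show that sites will in fact stop at 80, and if they recruit about 94 the stated power holds. The loss is moderate, but the stopping rule as written does not deliver the plan's own figure.

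**What to change.** In Recruitment {15} and in the research framework text, give about 94 as the number enrolled and randomised, and keep 80 as the number of completers required. In the Abstract and the Discussion it is enough to say which of the two numbers 80 refers to.

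If 80 randomised is really the cap, say so. State about 68 expected completers and about 73% power in the sample-size section, and redefine the second interim look, since 60 would then be about 88% of expected completers. If 94 is adopted, the interim trigger needs no change.

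**Cost.** If sites are already working to 94, this is a text correction. If they are working to 80, it means 94 − 80 = 14 more clients, each with a full course of sessions. At the slower enrolment rate it may also mean a short extension, about 0.75 months beyond the 11-month window. Restating the power avoids this cost but accepts the smaller trial.

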### Who will take informed consent? {26a}

Following initial screening interviews and administration of the Hamilton Depression Rating Scale-17 (score ≥ 20) and Generalized Anxiety Disorder Questionnaire-IV (score ≥ 5.7), eligible clients will undergo final eligibility assessment (see Eligibility Criteria). Therapists will notify all selected clients of their inclusion in the study. Clients will then receive the study information and consent materials. The therapists will obtain written informed consent from willing clients.

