## Methods: participants, interventions, and outcomes

### Study setting {9}

The present study will be conducted across multiple settings corresponding to the sequential three phases of the research.i.Phase one will be conducted through a narrative literature review, expert consultations (involving EMDR therapists) based in Pakistan. These activities will be carried out through a combination of in-person meetings and secure online platforms, depending on participant availability.ii.Phase two will be implemented in both online and in-person clinical settings at the selected clinics or psychotherapy centers located in the three selected cities in Pakistan, where the adapted DeprEnd EMDR therapy protocol will be delivered by four EMDR certified therapists. Data collection during this phase will occur through clinical assessments and standardized self-report measures.iii.Finally, phase three will be conducted as a multi-center randomized controlled trial study implemented in both online and in-person clinical settings at the selected clinics or psychotherapy centers located in the three selected cities in Pakistan, where the adapted DeprEnd EMDR therapy protocol will be delivered by four EMDR certified therapists. Data collection during this phase will occur through clinical assessments and standardized self-report measures. During this phase, process fidelity and adherence to the adapted DeprEnd EMDR protocol will be monitored at mid of therapy. 

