### Implementation {16c}

Following eligibility confirmation and baseline assessments (T_1_), randomization will be executed through the designated electronic platform (OpenClinica/Sealed Envelope) by a research assistant who will not be involved in outcome measurement. The online system will be connected to the therapists’ and patients’ emails. It will automatically notify the treating therapist of the allocated intervention mode (online or in-person) and inform the patient via secure messaging, while maintaining the blinding of outcome assessors. To ensure protocol fidelity, therapists will receive arm-specific procedure checklists corresponding to their notification. The principal investigator will conduct weekly cross-checks between the electronic allocation records and physical randomization documents to detect and rectify any discrepancies.

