## Assignment of interventions: blinding

### Who will be blinded {17a}

Due to the single blind-nature of intervention, complete blinding is not feasible for clients or therapists regarding delivery mode (online vs. in-person EMDR). However, therapists will remain blind until after completing the initial consultation with clients. Outcome assessors (research assistants) and data analysts will maintain full blinding throughout the trial. To minimize bias:Outcome assessors will perform clinical evaluations before therapy sessions begin and without access to subsequent treatment setting information.Data analysts will work with de-identified datasets using group codes.For fidelity analysis, independent reviewers will assess edited audio/video recordings with all platform-specific references removed.Blinding success will be empirically evaluated at the study midpoint by asking blinded personnel to guess group allocations, with ≤ 60% correct guesses indicating adequate maintenance of blinding.

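### Therapists who learn their own clients' allocations also notify clients and take consent before randomisation, so under minimisation by site they may guess the next arm somewhat better than chance

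*Protocol article*

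**What the plan says.** Under Who will take informed consent? {26a}, therapists act after screening and the final eligibility assessment: "Therapists will notify all selected clients of their inclusion in the study", and then "The therapists will obtain written informed consent from willing clients". The participant timeline {13} places consent and baseline assessment at the first time point. Sequence generation {16a} and Implementation {16c} place randomisation after baseline, so consent comes before allocation.

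After allocation, Implementation {16c} says of the electronic system: "It will automatically notify the treating therapist of the allocated intervention mode (online or in-person". Who will be blinded {17a} accepts that therapists cannot be blinded to delivery mode. For each new client, "therapists will remain blind until after completing the initial consultation with clients". Study setting {9} describes a therapy "delivered by four EMDR certified therapists" across three cities.

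Allocation is by minimisation. The algorithm in Sequence generation {16a} "assigns participants to the treatment arm that minimizes overall imbalance, with a probabilistic element", and its factors include study site. Concealment mechanism {16b} lists age instead and omits site. The article does not give the probability of assigning the balancing arm; it refers to Supplementary File A, which is not at hand.

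**The concern.** Minimisation tends to correct the running imbalance. Anyone who knows recent allocations in a group that the algorithm balances can guess which way the next one will lean. Hiding the system's output until baseline is complete does not prevent this, because the guess needs only past allocations. The notification step supplies these to the treating therapist one client at a time. Keeping therapists blind until after the initial consultation protects the current client's arm, not the arms of earlier clients.

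The same therapists, on the natural reading, hold the consent conversation. How and when a client is invited, and how hard a hesitant client is encouraged, could depend on the expected arm. Traits such as motivation or ease with technology are in neither factor list, so the allocation would not balance them. The primary contrast is the difference in HAM-D-17 change between arms against a 3-point margin, so a systematic difference in who enters each arm would feed directly into it.

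**Working it through.** **Inputs from the protocol.** 80 clients, 1:1 allocation, three centres, four therapists. Minimisation factors are site, gender, severity and comorbidity {16a}, or age, gender, severity and comorbidity {16b}. The SD of change is 8 and the margin is 3 points.

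**The plan's own figure.** The protocol states no figure for predictability. Its sample size, which sets the length of the simulated sequence, reproduces: 7.84 × 128 / 25 = 40.14 per arm, stated as 40, so 80 in total; 80 / 0.85 = 94.1, stated as 94.

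**Assumptions, not in the protocol.** The probability p of assigning the balancing arm is 0.60 to 0.95. Sites are of equal size. Gender, severity and comorbidity are binary at 50% each. Therapists are split 2/1/1 over the sites. The algorithm sums the marginal imbalances. The guesser names the arm under-represented so far, and a tie counts as 0.5. There were 300 simulated trials per setting. That is 300 × 80 = 24,000 guesses, so the simulation error is roughly √(0.25/24,000) = 0.3 percentage points.

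**Correct-guess rate for the next arm (chance = 50%).**

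| p | Site a factor: own clients only | Site a factor: whole-site totals | Same, when the site is unbalanced | Site not a factor: whole-site totals |
|---|---|---|---|---|
| 0.60 | 53.8% | 54.2% | 55.2% | 51.3% |
| 0.70 | 56.3% | 57.7% | 60.0% | 51.7% |
| 0.80 | 59.2% | 61.4% | 65.8% | 52.5% |
| 0.90 | 61.4% | 64.6% | 71.8% | 52.6% |
| 0.95 | 62.7% | 66.0% | 74.7% | 52.6% |

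Without site as a factor, also using the client's covariates raises the rate only to 51.9–53.9%. With 94 clients and p = 0.80, whole-site totals give 61.6%, so the recruitment target hardly matters.

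**Who has which knowledge.** The protocol supports the own-clients column. With four therapists and at least one per site, two sites would have a sole therapist, for whom own-client and whole-site knowledge coincide. At the shared site they coincide only if colleagues share allocations, which no section says.

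**Illustrative bias.** Let D be the difference in mean change between clients entered when online is expected and those entered when in-person is expected. Let g be the correct-guess rate. If every client is sorted by the guess, a share g of each arm was expected there and 1 − g was not, so bias = D × (2g − 1). With D = 2 points (assumed):

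- g = 0.54: 2 × 0.08 = 0.16 points, or 0.16/3 = 5% of the margin.
- g = 0.63: 2 × 0.26 = 0.52 points, or 17%.
- g = 0.66: 2 × 0.32 = 0.64 points, or 21%.
- Site not a factor, g = 0.51 to 0.54: 0.04 to 0.16 points.

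The sign depends on which clients are steered towards which arm.

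**The case against.** The protocol has real safeguards. Randomisation is central and run by an independent research assistant, with a random element included to reduce predictability. Only the next assignment is released, after baseline. Client selection {14} and Recruitment {15} require consecutive enrolment of every eligible client. Therapists act after eligibility has been assessed, and no section says that they decide eligibility. The looser entry terms, such as treatment-naive status being a preference, are therefore not shown to be theirs to apply. All this stands, and it makes steering a limited opportunity rather than a demonstrated practice. It does not remove the route, because entry still depends on the client being willing and the therapist conducts that conversation.

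Four stronger readings are tempting and are not supported:

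- A reader might infer that therapists know every earlier allocation at their site. The system notifies only the treating therapist. Someone who knew all sites and all covariates would guess correctly 59–88% of the time, but no section gives therapists that knowledge.
- A reader might conclude that prediction is well above chance. That depends on p, which is not shown, and on which factor list applies. Near-chance guessing is also consistent with the text.
- A reader might compare these rates with "≤ 60% correct guesses indicating adequate maintenance of blinding". That limit concerns blinded personnel guessing allocations at the study midpoint. It is not a tolerance for unblinded therapists predicting the next assignment.
- A reader might convert the bias into a raised false non-inferiority rate. That needs a 2-point difference with no source in the protocol, every client sorted by the guess, and steering that favours online. Steering the other way would make non-inferiority harder to show.

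**Conclusion.** The concern holds in a limited form. Therapists who learn their own clients' allocations and cannot be blinded to mode also notify clients and take consent before randomisation, and central release of the next assignment does not close that route. That the consenting therapists are the four treating therapists is an inference, but the natural one.

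If site is a minimisation factor, the gain over chance is about 4 to 13 percentage points from own clients and 4 to 16 from whole-site totals. If it is not, the gain is about 1 to 4 points. These figures rest on the assumed p of 0.60–0.95 and the other simulation settings. The bias of about 0.2–0.6 points is a worst-case illustration of unknown direction, not an estimate. This is a weakness worth closing because it is cheap to close. It is not evidence that the comparison is biased.

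**What to change.** In Who will take informed consent? {26a}, assign eligibility sign-off, notification of inclusion and consent to the arm-blinded research assistants who already give the clinical ratings under Plans for assessment {18a}. The assistant who runs randomisation should not do this. Record and lock the eligibility decision and consent in the central system before randomisation. Keep the therapists' blind initial consultation described in {17a}, placed after consent is locked. Reconcile the factor lists in {16a} and {16b}.

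If the person taking consent knows no earlier allocations, the correct-guess rate is 50% by construction, whatever p or factor list applies.

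The cost is some research-assistant time and a procedural amendment. The trial status section says that recruitment began on 1 April 2025 and is under way, so the change protects only clients not yet enrolled. For those already entered, the overlap of roles should be disclosed when the trial is reported.
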